**Day 60 (+/- 14 days) Postrandomization Follow-up Assessment—site clinic visit or telephone call:**

- Relevant interval medical history (including symptoms and concomitant medications) since last assessment will be obtained, including death, MI, major complications from cardiovascular procedure or testing (stroke, major bleeding, anaphylaxis, renal failure), unstable angina hospitalization.
- Test images and stress ECGs from the first test (and the randomized test, if different) will be uploaded to the DTCC. If applicable, the subject's first invasive coronary angiography report and images will be uploaded to the DTCC. All clinical test reports will be sent to the CCC at the DCRI.
- The results of any additional noninvasive tests or invasive catheterizations performed within the first 60 days will be collected.
- Radiation exposure will be assessed.
- Interval resource consumption, including hospitalizations, will be assessed.
- Patient satisfaction will be assessed.

**Follow-up at 6 months postrandomization and every 6 months thereafter will be conducted by DOFG staff or its trained designees:**

- Relevant interval medical history (including symptoms and concomitant medications) since last assessment will be obtained, including death, MI, major complications from study-related cardiovascular procedures (e.g. catheterization, PCI, CABG, CTA, stress echo, stress nuclear) or testing (stroke, major bleeding, anaphylaxis, renal failure), unstable angina hospitalization.
- Interval radiation exposure will be assessed.
- Interval resource consumption, including hospitalizations, will be assessed.
- Cardiovascular risk modification will be recorded.
- QOL questionnaires will be completed at 6 months, 12 months, and 24 months post-randomization (among patients followed for 24 months).

---

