### **7.2.5 Secondary Endpoint #5**

Incidence of:

- Invasive cardiac catheterization without anatomic obstructive CAD

This endpoint is defined in Section 7.2.1 above. By definition, the only patients who can experience this endpoint (catheterization without obstructive CAD) are those who undergo a cardiac catheterization within 90 days following randomization. All other patients (those who have a catheterization which reveals anatomically obstructive CAD ( $\geq 50\%$  stenosis), and those followed for at least 90 days after randomization who do not undergo cardiac catheterization in that time interval clearly do not meet this endpoint. Although the major interest is simply whether or not an invasive catheterization without obstructive CAD occurred within 90 days following randomization (irrespective of the timing when it occurred), the analysis can be complicated by the fact that some patients may die or withdraw consent prior to the 90-day time-point and therefore are not observable for the entire 90-day period. While the number of such patients is

expected to be small, they will be properly taken into account by using the Fine-Gray competing risk methodology described in section 7.2.4 above as implemented in the SAS procedure PHREG. Patients whose length of follow-up is more than 90 days (which will be most of the study patients) will be censored at 90 days in this analysis. The 90-day cumulative incidence rate of this event for each randomized arm will be calculated as part of the analysis to aid in the interpretation of the results.

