### 7.2.7 Secondary Endpoint #7

- Cumulative radiation exposure

The radiation exposure endpoint (as described in Section 3.2) is defined as the cumulative radiation exposure from all cardiovascular diagnostic testing and procedures related to testing or management of atherosclerotic CAD and performed within 90 days following randomization. The testing and procedures will include CTA, stress nuclear imaging, diagnostic cardiac catheterization, and catheterization with percutaneous coronary intervention (PCI). For each patient, the amount of radiation exposure will be calculated as detailed below.

- a. For the initial diagnostic test (either CTA or stress nuclear imaging), radiation exposure for each patient was measured by the sites and documented by the Diagnostic Testing Coordinating Center (DTCC) using standard methodology.
- b. Radiation exposure for all subsequent diagnostic tests (CTA or nuclear imaging) will be estimated using multiple imputation based on the type of test performed, the CTA scanner or tracer protocol (if available), the radiation exposure as observed for the initial tests in the trial, and patient demographics.
- c. For patients undergoing cardiac catheterization, radiation will be estimated (imputed) based on data from the literature. The imputed value will depend on whether the catheterization was diagnostic only (in which case the imputed value will be 7mSv), or whether a PCI was performed (in which case the imputed value will be 15 mSv).

Handling Missing Data: Any patients with missing radiation data for the initial diagnostic test will have their exposure estimated using multiple imputation as in (b) above based on the diagnostic test received and the radiation exposure measurements available from the other patients. If a patient did not undergo any diagnostic test or cardiac procedure, their radiation dose will be zero.

Specific Analyses:

- (1) Comparison of the diagnostic testing arms as randomized with respect to *cumulative radiation exposure from all cardiovascular diagnostic tests and procedures* performed within 90 days following randomization. Patients who did not undergo either a diagnostic test or cardiac procedure within 90 days or who underwent a functional test with no radiation will be assigned an exposure value of zero.

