- (2) Comparison of the diagnostic testing arms as randomized with respect to *radiation exposure of the initial diagnostic test* performed within 90 days following randomization. This comparison will include all randomized patients. Any patients who did not undergo either a CTA, a nuclear imaging test, or a cardiac catheterization as the initial diagnostic test performed within the 90-day period will be assigned an exposure value of zero.

- (3) Comparison of radiation exposure of the initial diagnostic test *according to the initial non-invasive test performed* (CTA vs. nuclear imaging). This comparison will be performed (i) in all patients whose initial diagnostic test was either CTA or nuclear imaging, and (ii) in patients undergoing either test in the randomization stratum consisting of patients where the enrolling site specified that if the patient was randomized to a functional test, stress nuclear imaging would be performed.

Statistical Methods: The distribution of cumulative radiation exposure in each randomized arm will be descriptively summarized (using means and standard deviations, medians, percentiles, and cumulative distribution functions) and statistically compared between the randomized arms and between different testing modalities using appropriate two-sample test methodology.

There is a sub-study within PROMISE on radiation exposure (PROMISE-SAFER) in which the radiation exposure data will be analyzed in greater detail. PROMISE-SAFER will have a separate analytic plan developed by the DCRI and the SAFER investigators at Columbia University.

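### SAP 7.2.7 has no rule for patients who withdraw or are lost before day 90, so those with no known test default to zero radiation

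*Supplement*

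**What the plan says.** SAP 7.2.7 (Secondary Endpoint #7) sums the dose from cardiovascular tests and procedures within 90 days of randomization. Its missing-data paragraph has two parts:

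- Imputation: "Any patients with missing radiation data for the initial diagnostic test will have their exposure estimated using multiple imputation". The imputation is based on the test the patient received, so that test must be known.
- Zero: "If a patient did not undergo any diagnostic test or cardiac procedure, their radiation dose will be zero".

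Analysis (1), cumulative exposure, repeats the zero rule for two kinds of patient: "Patients who did not undergo either a diagnostic test or cardiac procedure within 90 days", and any who "underwent a functional test with no radiation will be assigned an exposure value of zero". It does not require that the patient was followed for the 90 days. Of analysis (2), dose of the initial test, the SAP says: "This comparison will include all randomized patients".

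SAP 7.2.5 (Secondary Endpoint #5) uses the same window. It notes that "some patients may die or withdraw consent prior to the 90-day time-point and therefore are not observable for the entire 90-day period", expects few of them, and says that "they will be properly taken into account by using the Fine-Gray competing risk methodology". SAP 7.2.7 has no counterpart.

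On data collection, protocol Amendment 2, section E2, says of the day-60 visit: "The results of any additional noninvasive tests or invasive catheterizations performed within the first 60 days will be collected". The next scheduled contact is at 6 months.

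**The concern.** A patient who withdraws or is lost before day 90 may have no test on record. That patient cannot have a dose imputed, because no test is known, and is not removed from analysis (2). The only value left is zero.

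That zero is often likely to be false. Every patient enters with noninvasive testing already planned, and protocol section D2 expects testing to go ahead whether or not the patient joins the trial. Someone who withdraws untested may well be tested elsewhere, unseen by the trial.

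A smaller version of the problem affects patients who have a recorded first test and are then lost. Tests between the day-60 visit and day 90 come to light only at the 6-month contact. If that contact fails, any exposure in those weeks counts as none.

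SAP section 18 lists radiation safety, in last place, among the results on which the trial's impact rests. Patients know which test they were assigned, so withdrawal could differ by arm.

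**Working it through.** The documents give no effect size, standard deviation or power for radiation, so there is no stated figure to reproduce. The size of the problem can only be bounded.

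**Inputs**

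- Dose per CTA or nuclear test: 7 to 17 mSv, with CTA reducible to about 2 to 6 mSv (protocol D3, 3.g).
- Nuclear share of functional tests: 61%, from a claims database (protocol C5). The trial's own share may differ.
- Loss to follow-up: up to 3% (protocol F1). It is not specific to the first 90 days, so it is used here as an upper limit.
- Patients per arm: 5,000 (protocol F1). So 3% is 150 patients per arm.
- Assumptions: one initial test per patient, no catheterization dose, and all loss before the test. The last is a worst case, since the test is due within 30 days.

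**Formula.** Let mC be the mean CTA-arm dose and mF = 0.61 × (nuclear dose) the mean functional-arm dose. Let dC and dF be the shares who would have been tested but are unobserved and scored zero. Then

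observed difference = (1 − dC)·mC − (1 − dF)·mF

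bias = −dC·mC + dF·mF

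**Equal loss, d in each arm.** The observed difference is (1 − d) times the true one.

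- CTA 17, nuclear 17: mF = 10.37 and the true difference is 6.63. At 3% it becomes 6.43; at 1%, 6.56.
- CTA 12, nuclear 12: mF = 7.32 and the true difference is 4.68. At 3% it becomes 4.54.

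**Loss in one arm only, 3%**

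| Arm with loss | Dose 7 mSv | Dose 17 mSv |
|---|---|---|
| CTA | −0.03 × 7 = −0.21 | −0.03 × 17 = −0.51 |
| Functional | +0.03 × 4.27 = +0.13 | +0.03 × 10.37 = +0.31 |

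**Direction.** With equal loss, the zeros take more dose from the CTA arm only if mC exceeds 0.61 times the nuclear dose. With CTA at 6 and nuclear at 12 mSv, the true difference is 6 − 7.32 = −1.32. At 3% loss it becomes −1.28, so the functional arm loses more dose.

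**Against sampling error.** SE = SD × √(2/5000) = 0.02 × SD. For an assumed SD of 5 to 10 mSv this is 0.10 to 0.20 mSv. The largest one-sided biases exceed it. Equal loss in the 12/12 example gives 0.14 mSv, of the same order.

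**Where it does not arise.** Analysis (3) covers only patients whose initial test was CTA or nuclear imaging, so the zero rule does not enter.

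**The case against.** The strongest reply is textual. The SAP assigns zero to patients who did not undergo a test, and for them zero is the true dose. A reader might infer that it orders zero for anyone without a recorded test, including those who withdrew, were lost or died. No sentence says so. This part of the reply stands: the fault is a missing rule. But after withdrawal an analyst cannot tell untested from unobserved, and 7.2.7 offers no third category, so the default remains.

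Death does not belong in the concern. A patient who dies receives no further dose, so the dose to death is the true cumulative value.

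A reader might also infer that the comparison is biased against finding more radiation with CTA, perhaps materially. The documents do not support that. The low CTA doses in protocol 3.g can reverse the direction. At 12 mSv per test, a split such as 5% lost on CTA and 2% on functional testing would give −0.60 + 0.15 = −0.45 mSv, about 10% of 4.68. Nothing in the documents supports that split, and 5% exceeds the 3% allowance. SAP 7.2.5 expects few patients to be unobserved before day 90.

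Finally, SAP 7.2.7 refers to a separate plan for a radiation sub-study (PROMISE-SAFER), which is not shown and may contain a rule. Even so, 7.2.7 defines the trial's own endpoint, and the rule should be stated there.

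**Conclusion.** The gap is real and the point is minor. For patients who withdraw or are lost before day 90 with no known test, the stated rules lead to 0 mSv, although the protocol expects such patients to be tested. The SAP addresses incomplete observation of the same 90 days in 7.2.5 but not here.

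Under the worst-case assumptions above, equal loss shrinks the mean difference by at most 3% of itself, and one-sided loss of 3% shifts it by about −0.51 to +0.31 mSv. True differences over the 7 to 17 mSv range run from about −3.4 (7 − 10.37) to +12.7 mSv (17 − 4.27), so reversal of a clear result is unlikely. A bias well above sampling error needs strongly unequal loss. These figures are for means; the SAP leaves the two-sample test open, and a rank test would be affected differently in detail.

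**What to change.** In SAP 7.2.7:

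1. Assign zero only to patients with documented follow-up to day 90, or death before it, and no test or procedure involving radiation.
2. For patients who withdrew or were lost before day 90, treat the unobserved part of the window as missing. Keep any dose already recorded.
3. Extend the planned multiple imputation to that part, covering whether a test was done, its type and its dose. Use arm, the functional test chosen before randomization, and demographics.
4. Report the number of patients affected, by arm.
5. Give two sensitivity analyses: one with all such patients at zero, and one that does not assume the assigned test was received. The second matters because a patient who left to avoid the assigned test would otherwise tend to be imputed that same test.

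The cost is a few sentences and a modest extension of an imputation model already planned. The downsides are a slightly wider interval and reliance on a missing-at-random assumption, which the second sensitivity analysis probes.

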## **C5 *Rationale for Selection of Testing in Each Experimental Arm***

### ***Functional Testing Arm: Stress Nuclear, Stress Echo, and Exercise ECG***

Each of these procedures is a well-established and accepted strategy to diagnose CAD. Each has also been in routine clinical use for over 20 years and is well supported by class I, level of evidence B ACC/AHA practice guideline recommendations for use in suspected CAD. The guidelines further document specific indications as well as diagnostic and prognostic performance. (See also Table 2.) A national claims database (United HealthCare) documenting contemporary U.S. testing patterns shows that stress

---

nuclear exams constitute 61% of tests, with stress echo at 18% and exercise ECG at 21%. Computed tomographic angiography and stress magnetic resonance imaging comprised less than 1% each. Seventy-nine percent of tests were performed with exercise stress. The lack of a single dominant diagnostic strategy for current practice, even in this insured population, highlights the essential need for flexibility and breadth in the choice of functional tests to fully reflect real-world diagnostic practices and maximize generalizability and clinical impact. Thus it is essential that exercise ECG, stress echo, and stress nuclear imaging are all included in the functional testing arm.

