### 3.2 Secondary Objectives

The secondary objectives are to compare the following clinical, economic, and quality-of-life outcomes in subjects randomized to initial anatomic versus functional diagnostic testing:

1. Composite endpoint consisting of each of the components of the primary endpoint plus the addition of an invasive cardiac catheterization without obstructive CAD (as defined below in secondary objective #5)
2. Death or myocardial infarction or unstable angina hospitalization
3. Death or myocardial infarction
4. Major complications from cardiovascular procedures and testing (stroke, major bleeding, anaphylaxis, and renal failure requiring dialysis)
5. Invasive cardiac catheterization without obstructive CAD (defined as no stenosis  $\geq 50\%$  in any major epicardial vessel, including side branches  $\geq 2\text{mm}$  in diameter, on the first catheterization performed  $\leq 90$  days after randomization)
6. Medical costs, resource use, and incremental cost effectiveness
7. Radiation exposure (defined as cumulative radiation exposure of all cardiovascular tests or procedures related to testing or management of atherosclerotic CAD and performed within 90 days following randomization)
8. Health related quality of life

To aid in the interpretation of the primary and secondary endpoint comparisons, the individual components consisting of (a) death and (b) myocardial infarction will also be compared between the anatomic and functional testing arms.

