## **18. Overall Interpretation and Impact of PROMISE**

Although Sections 3.1 and 3.2 list the primary objective and eight different secondary objectives of the trial, the overall impact and interpretation of the trial will be based on the results of the analyses, in the following order:

- Primary endpoint – superiority assessment
- Primary endpoint – non-inferiority assessment (if needed)
- Secondary endpoint #1: Primary endpoint plus invasive cardiac catheterization without obstructive CAD
- Economic outcomes
- Radiation safety

While the analyses of secondary clinical endpoints 2 through 5 listed in Section 3.2 will be important and are certainly of great interest, those endpoints are components (building blocks) of the primary endpoint and secondary endpoint #1. Therefore, a major role of those secondary analyses will be to aid in the interpretation of the analysis of the primary endpoint and key secondary endpoint #1. The real impact of the trial will rest upon the results of the analysis of the primary endpoint, followed by the outcome of key secondary endpoint #1, followed by the economic outcomes and then the radiation safety results. All other analyses will be ancillary and supportive of those pivotal results.

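### The zero-dose sentence in SAP 7.2.7, analysis (1), contradicts the cumulative radiation endpoint it serves, because it lacks the words that limit it to patients with no radiating test or procedure

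*Supplement*

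**What the plan says.** SAP 7.2.7 states that the endpoint is "defined as the cumulative radiation exposure from all cardiovascular diagnostic testing and procedures related to testing or management of atherosclerotic CAD" performed within 90 days of randomization. SAP 3.2 words it almost identically: "cumulative radiation exposure of all cardiovascular tests or procedures related to testing or management of atherosclerotic CAD and performed within 90 days following randomization". The items counted are CTA, stress nuclear imaging, diagnostic catheterization and catheterization with PCI.

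Three steps supply the dose:
- (a) The initial CTA or nuclear test has its dose measured by the site.
- (b) "Radiation exposure for all subsequent diagnostic tests (CTA or nuclear imaging) will be estimated using multiple imputation".
- (c) A catheterized patient is given 7 mSv if the procedure was diagnostic only, or 15 mSv if PCI was performed.

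None of these steps makes an exception for a patient who also had a stress echo or exercise ECG.

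Zero is assigned in three places. The missing-data paragraph gives it to patients with no test and no procedure. Analysis (2), on the initial test alone, gives it to patients whose initial test was not a CTA, nuclear scan or catheterization. Analysis (1), on the cumulative dose, gives it to patients with neither a test nor a procedure within 90 days "or who underwent a functional test with no radiation will be assigned an exposure value of zero".

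SAP 18 ranks what the trial's impact rests on: the primary endpoint, then key secondary endpoint #1, "followed by the economic outcomes and then the radiation safety results".

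**The concern.** Analysis (1) differs from analysis (2) in that it captures dose downstream of the first test. Its closing sentence, taken at face value, makes a non-radiating functional test sufficient for a total of zero, whatever else happened in the 90 days. The sentence joins two conditions with an or. The first mentions cardiac procedures and the second does not.

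Patients who meet the second condition and also have real dose are to be expected. Section D3 3.b of protocol Amendment 2 leaves further functional, anatomic or invasive testing to the care team. SAP 12 expects a small percentage of patients in each arm to receive the other arm's test first.

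A programmer who follows the sentence and one who follows the definition would produce different datasets for an endpoint that SAP 18 names among the trial's pivotal results.

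**Working it through.** The plan states no figure that depends on this rule, so there is none to reproduce. The check has two parts.

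**1. The two rules applied to the same records**

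| Record within 90 days | Definition with steps (a)–(c) | Closing sentence of (1), read literally |
|---|---|---|
| No test, no procedure | 0 | 0 |
| Stress echo only | 0 | 0 |
| Exercise ECG, then diagnostic catheterization | 7 mSv | 0 |
| Stress echo, then catheterization with PCI | 15 mSv | 0 |
| CTA, then stress echo | the CTA dose | 0 |

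The rules agree when there is no dose to sum. They disagree whenever a non-radiating functional test occurs together with a radiating test or procedure. Analysis (2) does not have this problem, because its zero rule names the radiating tests whose absence is required.

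**2. How much dose a literal program could lose**

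Mean dose lost per patient in an arm = (share with a non-radiating functional test who also had a radiating test or procedure) × (dose).

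Inputs from the documents:
- 5,000 patients per arm (protocol F1).
- 7 and 15 mSv for catheterization (SAP 7.2.7).
- 7 to 17 mSv for nuclear and CTA, with CTA reducible to about 2–6 mSv (protocol D3 3.g).
- 18% stress echo and 21% exercise ECG among functional tests, together 39% (protocol C5). These shares come from a US claims database cited as background. Applying them to this trial is an assumption.

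The overlap shares are assumptions throughout, because the documents give none.

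*Functional arm.* 0.39 × 5,000 = 1,950 patients with echo or exercise ECG. If a fraction f of them is also catheterized:

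| f | Patients zeroed | Loss in arm mean, 0.39 × f × 7 to 0.39 × f × 15 |
|---|---|---|
| 5% | 98 | 0.14 to 0.29 mSv |
| 10% | 195 | 0.27 to 0.59 mSv |
| 20% | 390 | 0.55 to 1.17 mSv |

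This counts catheterization only. It omits a second, radiating scan after echo or exercise ECG, and nuclear patients who later have one of those tests.

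*CTA arm.* If a fraction g of patients has both a CTA and a non-radiating functional test, with a CTA dose between 2 and 17 mSv:

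| g | Patients zeroed | Loss in arm mean, g × 2 to g × 17 |
|---|---|---|
| 1% | 50 | 0.02 to 0.17 mSv |
| 5% | 250 | 0.10 to 0.85 mSv |
| 10% | 500 | 0.20 to 1.70 mSv |

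*Net effect.* The shift in the CTA-minus-functional mean equals the functional-arm loss minus the CTA-arm loss. The extremes over these ranges are:
- 0.39 × 0.05 × 7 − 0.10 × 17 = 0.14 − 1.70 = −1.56 mSv
- 0.39 × 0.20 × 15 − 0.01 × 2 = 1.17 − 0.02 = +1.15 mSv

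The range spans zero. If the sentence is taken to mean only non-radiating testing, the loss is 0 in both arms.

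**The case against.** The strongest reply is that nobody would apply the sentence literally. The endpoint covers all tests and procedures, catheterization and PCI are named as counted, and steps (b) and (c) assign dose without exception. The missing-data paragraph reserves zero for patients with no test or procedure. Analysis (1) itself opens as a comparison of exposure from all tests and procedures. In that setting the sentence most naturally names two groups with nothing to sum: those not tested at all, and those whose only testing was non-radiating. It is also fair to say that radiation comes last in the SAP 18 ordering, and that a separate plan for the PROMISE-SAFER sub-study will treat the radiation data in more detail.

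Most of this stands. A reader might infer from the sentence that the plan discards real dose and that the reported difference between the arms is biased. The documents do not support that inference. They show no decision to drop downstream dose, and they give no overlap rates from which a bias could be calculated.

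What survives is narrower. The argument from context works only by setting the sentence's wording aside, which confirms that the sentence disagrees with its own section. The sub-study plan does not settle the matter, because 7.2.7 itself specifies this comparison.

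**Conclusion.** The closing sentence of analysis (1) is internally inconsistent with the endpoint definition in SAP 3.2 and 7.2.7 and with steps (b) and (c). It is more than a missing detail: it is a stated derivation rule that returns a wrong value for ordinary care pathways if coded as written. The likely intent is the limited meaning, under which no dose is lost.

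Under literal coding, downstream dose would be lost in the functional arm, and CTA dose would be lost in CTA-arm patients who also have an echo or exercise ECG. The 0.14–1.17 mSv fall in the functional-arm mean is illustrative. It rests on a claims-database test mix and an assumed 5–20% catheterization overlap. It is tempting to go further and say which arm would be favoured. The two losses offset each other, and the illustrative net shift runs from −1.56 to +1.15 mSv, so the documents fix neither its size nor its sign. The effect on medians or rank comparisons was not calculated.

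**What to change.** Replace the closing sentence of analysis (1) in SAP 7.2.7 with:

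> Cumulative exposure is the sum of the doses from (a)–(c) over every CTA, nuclear test, catheterization and PCI within 90 days of randomization. A non-radiating functional test contributes 0 to this sum. The total is zero only for patients with no radiating test or procedure in that period, including those whose only testing was non-radiating.

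Leave analysis (2) unchanged, since its zero rule is already limited to the initial test. The change costs one sentence in the SAP and a check that the derivation program follows it. No new data are needed, and no result changes if the limited meaning was intended all along.
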